##### Iowa infant feeding attitude scale (IIFAS)

The IIFAS will be used to assess maternal feeding attitude. This scale includes 17 items developed by Mora and colleagues [28]. The items incorporate a five-point Likert scale with categories of “strongly disagree” (1), “disagree” (2), “being neutral” (3), “agree” (4), and “strongly agree” (5). Nine items (numbers 1, 2, 4, 6, 8, 10, 11, 14 ,17) are reverse-scored while others are positively scored. The total final score ranges from 17 (showing negative breastfeeding attitude) to 85 (indicating positive breastfeeding attitude). The original scale showed good reliability with Cronbach’s ranging from 0.68 to 0.86 and good validity [28]. In the current study, a Chinese version of the IIFAS is used and indicates moderate reliability with Cronbach’s α ranging from 0.589 to 0.685 and good validity with 0.996 [29].

##### Breastfeeding knowledge questionnaire (BKQ)

The BKQ is used to assess breastfeeding knowledge of maternal women. The questionnaire includes 18 items and was modified based on previous literature [30] by Ouyang et al. [31]. It is a closed-ended questionnaire with true or false responses and had good internal reliability with Cronbach’s α = 0.93 [31]. The common use in previous studies [31, 32] was calculating the percentages of true or false of each item. In this study, the researchers imply true as “1”and false as “0” and will then calculate the total score of the 18 items of each participant.

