##### Postpartum specific anxiety scale-chinese version (PSAS-CN)

The Postpartum Specific Anxiety Scale (PSAS) was introduced in Turkey in 2016 by Assistant [name] [45]. The Chinese version was translated and revised by Xu et al. [46]. The scale consists of 50 items and contains four dimensions: (1) maternal competence and attachment anxiety; (2) infant health and safety; (3) infant care anxiety; and (4) mother’s psychosocial adjustment. The scale is a 4-point scale, with scores from 1 to 4 indicating “not at all,“ “occasionally,“ “often,“ " usually,“ and “always”. The higher the score, the more severe the symptoms of postpartum-specific anxiety. The scale has good reliability and according to Fallon et al. [45], and a score of 112 and above indicates a clinical level of anxiety. The Cronbach’s α coefficient for this scale is 0.95 [47].

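### As written, the BKQ rule credits the answer 'true', not the correct answer, and the PSAS-CN description gives five response labels for four scores

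*Protocol article*

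**What the plan says.** **BKQ** (protocol article, section on the Breastfeeding knowledge questionnaire). The purpose is stated: "The BKQ is used to assess breastfeeding knowledge of maternal women". So are the length and format: "The questionnaire includes 18 items" and "It is a closed-ended questionnaire with true or false responses". Earlier studies are said to have reported the instrument by "calculating the percentages of true or false of each item". The trial then sets its own rule, applied to all 18 items: "the researchers imply true as “1”and false as “0” and will then calculate the total score". The section mentions no answer key, no reverse-keyed items and no scoring by correctness.

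**PSAS-CN** (section on the Postpartum specific anxiety scale, Chinese version). The scale has 50 items. The text says "The scale is a 4-point scale, with scores from 1 to 4 indicating" and then names five labels: 'not at all', 'occasionally', 'often', 'usually' and 'always'. It adds, from a cited source, that "a score of 112 and above indicates a clinical level of anxiety".

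**Use.** The Statistical analysis section compares both scales between groups and over time by repeated-measures ANOVA. Maternal knowledge is named in the Aim, and the four lectures in Table 2 teach it.

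**The concern.** A knowledge score should rise when a woman answers more items correctly. A rule that gives the point to the response 'true' does this only for statements that are in fact true. For a false statement, a woman who has learned to reject it loses a point and one who wrongly accepts it gains one. If the questionnaire mixes true and false statements, learning on the two kinds of item pulls the total in opposite directions, and a real effect of the lectures on knowledge could be shrunk or hidden.

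For the PSAS-CN, five answers cannot be matched one-to-one with four scores. Whoever sets up the coding must drop a label or merge two, and the article does not say which. The total depends on that choice, and so does any classification against a fixed value such as 112.

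**Working it through.** **What can be reproduced.** The article states no BKQ range and no PSAS-CN range, and 112 comes from a cited source, so none of these can be rebuilt from its inputs. Two other scales serve as a check that the descriptions are otherwise coherent:
- IIFAS: 17 items scored 1–5 gives 17 × 1 = 17 to 17 × 5 = 85, as stated.
- BSES-SF: 14 items scored 1–5 gives 14 to 70, as stated.

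The IIFAS section also lists its nine reverse-scored items by number, so the article does specify keying where it intends it.

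**BKQ.** Inputs: 18 items, binary answers, 'true' = 1 and 'false' = 0 (all from the BKQ section). Assumption: k of the 18 items have 'false' as the correct answer. The article does not give k, so a range from 0 to 9 is shown.

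- Fully correct respondent, literal rule: (18 − k) × 1 + k × 0 = 18 − k.
- Respondent who answers 'true' throughout: 18, whatever she knows.
- Expected total if each item is answered correctly with probability p: (18 − k)p + k(1 − p) = k + (18 − 2k)p.
- Change when p rises by 0.20 (for example from 0.60 to 0.80): 0.2 × (18 − 2k).
- Change when items are scored by correctness: 0.2 × 18 = 3.6 for every k.

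| k (assumed) | Perfect knowledge, literal rule | Gain shown, literal rule | Gain scored by key |
|---|---|---|---|
| 0 | 18 | 0.2 × 18 = 3.6 | 3.6 |
| 3 | 15 | 0.2 × 12 = 2.4 | 3.6 |
| 6 | 12 | 0.2 × 6 = 1.2 | 3.6 |
| 9 | 9 | 0.2 × 0 = 0 | 3.6 |

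The literal rule is harmless only at k = 0.

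**PSAS-CN.** Inputs: 50 items, scores 1–4, five labels, and the value 112 (all from the PSAS-CN section).
- Range with scores 1–4: 50 × 1 = 50 to 50 × 4 = 200.
- 112 corresponds to an item mean of 112/50 = 2.24 and lies (112 − 50)/150 = 41.3% of the way up that range.

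To see whether the unresolved label matters, assume a woman gives the five labels, in order, to 12, 20, 10, 5 and 3 of the 50 items. This pattern is illustrative and not from the article. Fitting five labels into scores 1–4 requires merging two neighbours:

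| Labels merged | Total |
|---|---|
| 'usually' and 'always' | 12 + 40 + 30 + 20 + 12 = 114 |
| 'often' and 'usually' | 12 + 40 + 30 + 15 + 12 = 109 |
| 'occasionally' and 'often' | 12 + 40 + 20 + 15 + 12 = 99 |
| 'not at all' and 'occasionally' | 12 + 20 + 20 + 15 + 12 = 79 |

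The same answers fall above 112 under one merging and below it under the other three.

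**The case against.** **BKQ.** The strongest reply is that 'true' loosely means 'correct'. The sentence is awkwardly phrased, the instrument is meant to measure knowledge, and the per-item percentages of earlier studies can be read as percentages right and wrong. On that reading the rule is sound. Nor does the article show that any item is keyed 'false', and if none is, the literal rule does no harm. This stands as far as it goes: a reader might infer that the trial's knowledge scores will be wrong, and the document does not support that. It does not rescue the wording. The section uses 'true' and 'false' first for the answers a woman gives and then for the codes, and never says that the meaning has changed.

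**PSAS-CN.** The article says twice that the scale has four points, so the fifth label may be a slip in the prose, with the instrument itself having four options. That is plausible. A reader might infer that the scale could be coded 1–5, with a range of 50–250, but no such coding appears anywhere. A reader might also infer that a rate of anxiety based on 112 is a planned outcome. The article reports 112 from its source without adopting it for this trial, whereas the EPDS section expressly adopts its threshold of 10. The repeated-measures ANOVA does not depend on a cut-off.

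**Safeguards.** The data collector is to be trained in coding each item, and the Data management section foresees lists of valid codes with their meanings. An answer key could well sit in a codebook, and its absence from an article is no fault. The point here is different: the article states one rule that is wrong if followed literally and one description that contradicts itself. A codebook built from either would carry the problem forward.

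**Conclusion.** The concern holds in a limited form. The BKQ rule, read as written, measures agreement with the statements and would mis-score every item whose correct answer is 'false'. The size depends on k, which the article does not give: from no loss at k = 0 to complete loss of a uniform gain at k = 9, with two thirds lost at k = 6 (1.2 shown instead of 3.6). These figures also assume the same accuracy gain on every item.

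The PSAS-CN description is inconsistent on its face, with five labels for four scores. This leaves the scoring undefined; it does not show that scores will be wrong. The effect on classification at 112 is illustrated only for an assumed answer pattern, and matters only if the cut-off is used.

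Both scales are secondary outcomes. The primary outcome and the stated 76 per group are unaffected. The correction is worth making because knowledge is a named aim and both scales go into the planned analyses.

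**What to change.** **BKQ.** State that each item scores 1 if the answer matches the answer key and 0 if it does not, giving a total of 0–18, and place the key in the codebook. Handle missing answers by a separate, stated rule; whether a blank counts as wrong is its own decision and should not be settled by the coding of 'true' and 'false'.

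**PSAS-CN.** Check the response options of the Chinese version in use and make the labels agree with its scores of 1 to 4. Continue to analyse the scale as a score. If women are also to be classified at 112, say so, and do it only if that value was set on the same version and coding.

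**Cost.** A sentence or two per scale in the protocol and codebook, ideally before data entry. No extra participants or data are needed. If answers have already been entered, the BKQ can be re-scored as long as the item-level responses were kept.

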##### Breastfeeding self-efficacy Seale Short Form (BSES-SF)

Breastfeeding self-efficacy refers to the degree of confidence of mothers in their ability to breastfeed their infants. Breastfeeding Self-efficacy Scale (BSES) was developed by Dennis and Faux [33] in 1999 and was simplified in 2003 [34]. It was translated into Chinese by Liu et al. [35]. The Chinese version of the BSES-SF consists of 14 items with Cronbach’s α = 0.927. The scores’ range is 14 to 70 on a five-point Likert scale, with a score of 1 to 5 representing a range from “not at all” to “very confident”, with higher breastfeeding self-efficacy being associated with higher scores. The scale is divided into two dimensions: the skills dimension consists of nine items that measure the level of confidence in breastfeeding skills, and the personal internal reflection dimension of five items that measure attitudes and beliefs about breastfeeding.

##### Edinburgh postnatal depression scale (EPDS)

The EPDS is mainly used to assess the degree of postpartum depression. It was developed by Cox et al. [36], and translated into Chinese by Lee et al. [37] with a Cronbach’s α coefficient of 0.89, which showed good reliability and validity. In 2007, Guo et al. [38] translated and revised the scale according to the language habits of Chinese with a Cronbach’s α coefficient of 0.76 and the cut-off value of 9.5 [39]. It consists of 10 items, including mood, anxiety, fear, pleasure, self-blame, insomnia, coping ability, sadness, crying and self-harm. Each item has 4 points, and the total score is 30 points, with higher scores indicating more severe depression. In this study, postpartum depression was considered having a total score of ≥ 10 [40].

##### Social Support Rating Scale (SSRS)

The SSRS in a Chinses version was first developed by Xiao [41]. The scale included 10 items in three dimensions: objective support, subjective support and utilization of social support. The scores of items 1–4 and 8–10 are 1–4 points each. In item 5, the total score is scored with five options (A-E), ranging from “none “(1) to “full social support” (4). If the answer “none” in items 6 and 7 is scored for 0 points, and then the answer “other sources” is scored according to the number of sources. The scores of 35 and 45 are used as cut-off values to divide them into relatively low, general and relatively high social support. The Cronbach’s α coefficient ranged from 0.825 to 0.896, indicating good reliability of the scale [42].

##### Pregnancy-related anxiety questionnaire (PAQ)

The PAQ was developed by Chinese scholars Xiao Limin et al. [43] according to the characteristics of pregnant women in China, and is a self-assessment scale with 13 items using a 4-point scale ranging from 1 to 4. The Cronbach’s α coefficient and re-test reliability of the scale are 0.81 and 0.79, respectively. It focuses on three dimensions of worrying about the self (items 1–6), worrying about the health of the fetus (items 7–10, 13) and worrying about childbirth. The PAQ has no defined cut-off value while Zhang et al. [44] used the overall score of 75th percentile (P75) as the cut-off value for the presence or absence of pregnancy-related anxiety, i.e., 24 indicating the presence of pregnancy-related anxiety, otherwise it was none.

##### Postpartum specific anxiety scale-chinese version (PSAS-CN)

The Postpartum Specific Anxiety Scale (PSAS) was introduced in Turkey in 2016 by Assistant [name] [45]. The Chinese version was translated and revised by Xu et al. [46]. The scale consists of 50 items and contains four dimensions: (1) maternal competence and attachment anxiety; (2) infant health and safety; (3) infant care anxiety; and (4) mother’s psychosocial adjustment. The scale is a 4-point scale, with scores from 1 to 4 indicating “not at all,“ “occasionally,“ “often,“ " usually,“ and “always”. The higher the score, the more severe the symptoms of postpartum-specific anxiety. The scale has good reliability and according to Fallon et al. [45], and a score of 112 and above indicates a clinical level of anxiety. The Cronbach’s α coefficient for this scale is 0.95 [47].

#### Training and certification plans

Details of the data collection procedures are shown in Fig. 2. Collection will be completed by the same data collector, who will be trained on the study requirements, understanding of each questionnaire item, counseling for adherence and the eliciting of information from study participants in a uniform reproducible manner. The data collector will also be taught how to code each questionnaire item and how to enter data forms in the Excel spreadsheet. Each of the data collection forms and the nature of the required information will be discussed in detail on an item-by-item basis during a training session.

#### Participant withdrawal

Participants may withdraw from the study for any reason at any time. The investigator may also eliminate participants from the study in order to protect their safety and/or if they are unwilling or unable to comply with required study procedures after consultation with the researchers.

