### Sample size

The current EBF rate for infants under 6 months of age in China is 34.1% [3]. After the intervention, the rate is expected to increase to 60%, which was required by the *National Nutrition Plan (2017–2030)* [5]. Sample size was calculated for EBR in 6 months for a two-sided hypothesis test with a power of 90% and a significance level of 0.05. Therefore, according to the following formula, the study requires a minimum sample size of 76 (each group). Considering a 20% lost follow-up rate and 20% withdrawal rate because of failure to participate in the full intervention due to prematurity, a total of 218 participants will be needed for the study.$${n}_{1}={n}_{2}=\frac{{{[u}_{\alpha }\sqrt{2P\left(1-P\right)}+{u}_{\beta }\sqrt{{P}_{1}\left({1-P}_{1}\right)+{P}_{2}\left({1-P}_{2}\right)} ]}^{2}}{{(P1-P2)}^{2}}$$

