### Blinding

Allocation details will be placed in opaque and sealed envelopes by a study coordinator and concealed from recruiters, data collectors and the group allocator. After recruitment and baseline data collection, the other study coordinator will open the envelopes and allocated participants. Due to the nature of the intervention, intervention conductors and participants will not be blinded to group allocation. The data collector will be masked to group allocation during data collection and the statistician will also be masked during data analyses.

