#### Secondary outcomes

##### Maternal and neonatal morbidity outcomes

Maternal adverse lactation events include depressed nipples, breast milk stasis, acute mastitis, cracked nipples, breast swelling, breast eczema, and nipple trauma. The health status of infants will be investigated at 1-, 4- and 6-months postpartum by asking the mothers and their co-parents whether infants suffer from any conditions (eczema, anemia, diarrhea, and pneumonia). The height and weight of the infant at birth, 1 month, 4 months, and 6 months will also be investigated by questioning the mothers and co-parents.

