### Statistical analysis

Statistical analysis will be completed using SPSS (version 24.0). In order to compare the difference at baseline between the two groups, the two-sample t-test will be used for continuous variables and the χ^2^ test for classified data. Analyses of differences between two groups regarding maternal and neonatal morbidity outcomes, IIFAS, BKQ, BSES-SF, PAQ, PSAS-CN, EPDS and SSRS are evaluated in the same manner. In addition, one-way ANOVA analysis and two-sample t-test will be used to explore the influencing factors of the EBF rate. The data from the IIFAS, BKQ, BSES-SF, PAQ, PSAS-CN, EPDS and SSRS of the two groups at different time points (T0, T1, T2 and T3) will be tested using repeated measurement Analysis of Variance (ANOVA). For variables that have an interaction effect in repeated measurement ANOVA, a simple effect analysis will be carried out to further explore the effects of each factor. Cohen’s d will be reported to check the effect size. Cohen’s d will be used to evaluate the magnitude of difference between the two groups. According to the standard established by Cohen, the large, medium and small of the effect of d was divided into 0.8, 0.5, and 0.2 [48]. The randomized trial will use the statistical analysis “per protocol”. The significance level is set to less than 0.05 (double-tailed). P-values will be reported to four decimal places p-values and those less than 0.001 will be reported as p < 0.001.

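### The withdrawal rule and the sample-size allowance do not separate leaving the intervention from leaving follow-up, so obtainable feeding outcomes can be lost, probably more often in the intervention arm

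*Protocol article*

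**What the plan says.** Three sections of the protocol article bear on this.

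- **Participant withdrawal.** A woman may leave on her own initiative: "Participants may withdraw from the study for any reason at any time". The investigator may also remove her: "The investigator may also eliminate participants from the study in order to protect their safety and/or if they are unwilling or unable to comply". The compliance meant is with the procedures of the study, which are not defined further, and the researchers are to be consulted first. Both routes lead out of the study. The section names no route that ends only the intervention, and no other section says that outcomes are still sought after removal.
- **Sample size.** The allowance for losses reads: "Considering a 20% lost follow-up rate and 20% withdrawal rate because of failure to participate in the full intervention due to prematurity". Not completing the intervention is thus budgeted as withdrawal, separately from loss to follow-up.
- **Statistical analysis.** "The randomized trial will use the statistical analysis “per protocol" is the only analysis population named.

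Infant feeding pattern, the basis of the primary outcome, is collected at 1, 4 and 6 months postpartum. Infant illness and growth are obtained by asking mothers and co-parents. None of this requires attendance at an intervention session. The Control group section gives controls usual care and a contact at enrolment, with nothing further from the study team by way of guidance. The intervention arm has lectures, home visits, group counselling and individual counselling (Tables 1 and 2).

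**The concern.** Stopping an intervention and stopping observation are different events. When a plan merges them, outcomes that could have been collected are not, and no later choice of analysis set can bring them back.

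The merger matters here for two reasons. First, the grounds for removal arise after randomisation and mostly concern procedures that exist in one arm only. A control woman has no lecture or home visit to miss, and a preterm birth does not cut short any intervention for her. The loss is therefore likely to be heavier in the intervention arm. Second, women who miss sessions or deliver preterm may breastfeed exclusively less often than the rest. If so, removing them raises the observed rate in the arm that loses more of them, and the comparison leans towards the intervention. The plan states neither the imbalance nor the lower rate. The imbalance follows from the design; the lower rate is an assumption.

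**Working it through.** **1. The plan's own figure.** Inputs from Sample size: P1 = 0.341, P2 = 0.60, two-sided 0.05, power 90%. The pooled P is (0.341 + 0.60)/2 = 0.4705.

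n = [1.960 × √(2 × 0.4705 × 0.5295) + 1.2816 × √(0.341 × 0.659 + 0.60 × 0.40)]² / (0.259)² = (1.3835 + 0.8737)² / 0.0671 ≈ 75.9, so 76 per group. The stated figure reproduces. The total of 218 is matched by 76 × 1.2 × 1.2 = 109.4, taken as 109 per group. The incomplete-intervention 20% is therefore built into the recruitment target as if those women had no endpoint.

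**2. Which losses are avoidable.**

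| Reason for leaving | Can feeding status still be asked? |
|---|---|
| Misses intervention sessions, including through preterm birth | Yes |
| Removed by the investigator for safety | Yes, if she agrees to be contacted |
| Refuses the questionnaires, or withdraws consent to be contacted | No, under any rule |
| Cannot be reached | No |

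All components in Table 1 end by one month postpartum. After that the only study procedures described are the 4- and 6-month data collections, so non-compliance then means not answering. The avoidable loss therefore comes from removals up to about one month, but each can cost the outcomes at 1, 4 and 6 months.

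**3. Illustration of bias (assumed removal shares and rates).** Let the true exclusive breastfeeding rate be p = 0.341 in both arms, so there is no effect. Remove a share f of the intervention arm only, with rate e among those removed. The observed intervention rate is (p − f·e)/(1 − f), and the false difference is f(p − e)/(1 − f).

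| f | e = p/2 = 0.1705 | e = 0 (extreme) |
|---|---|---|
| 5% | 0.05 × 0.1705/0.95 = 0.9 points | 0.05 × 0.341/0.95 = 1.8 points |
| 10% | 0.10 × 0.1705/0.90 = 1.9 points | 0.10 × 0.341/0.90 = 3.8 points |
| 20% | 0.20 × 0.1705/0.80 = 4.3 points | 0.20 × 0.341/0.80 = 8.5 points |

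If e = p, or if removal is equal and equally selective in two arms with the same true rate, the false difference is zero.

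**4. Precision, for scale.** Of 109 per arm, 20% loss leaves about 87 (power 93.6% at the planned rates). Losing the second 20% as well leaves about 70 if the losses compound (109 × 0.64; power 87.4%) or about 65 if they add (109 × 0.60; power 85.2%).

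**The case against.** The best defence is that this is two sentences of ordinary withdrawal wording in a condensed article. Removal is discretionary and requires consultation, and the procedures in question include the questionnaires, so some of these women would be lost anyway. The fuller protocol may provide for follow-up after discontinuation. The Sample size text does not say that feeding status goes uncollected after a preterm birth; with a per-protocol analysis, that 20% may simply be exclusions from the analysis set. Much of this stands, and it limits the point to women removed for safety or for missed intervention sessions. It does not remove the point. The article states a rule, the rule is exit from the study, and nothing in it preserves the outcomes.

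A reader might infer more than the document supports:

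- **That 36% to 40% of women will lack a 6-month status because of this rule.** Those figures (1 − 0.8 × 0.8, or 20% + 20%) come from the sample-size allowance. No rate is given for investigator removals.
- **That following these women would bring worst-case bounds inside the effect sought (60 − 34.1 = 25.9 points).** It would not. With 20% missing in each arm, bounds on the difference are still 20 + 20 = 40 points wide.
- **That the women removed are those with mastitis, depression or early cessation.** Lactation events and depression are listed as outcomes ("Maternal adverse lactation events include depressed nipples, breast milk stasis, acute mastitis, cracked nipples, breast swelling, breast eczema, and nipple trauma", and the Edinburgh scale), but neither is named as a ground for removal.
- **That the removal decision is unmasked.** Under Blinding, "intervention conductors and participants will not be blinded to group allocation", but the section does not say whether the investigator who decides on removal is masked.

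**Conclusion.** The point holds in a limited form. As written, the plan allows obtainable outcomes to be lost when a woman leaves the intervention, and its recruitment target treats incomplete intervention through prematurity as loss of the participant. Because most procedures exist only in the intervention arm, the loss is likely to be uneven.

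The direction of bias, towards the intervention, depends on the assumption that the removed women breastfeed exclusively less often. The size cannot be estimated from the document. The illustration gives about 0.9 to 4.3 points for 5% to 20% removed from the intervention arm alone at half the average rate, against a planned effect of 25.9 points. That would not explain the whole planned effect, but it is avoidable. This is a cheap improvement to data collection, not a flaw that invalidates the design.

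**What to change.** 1. In Participant withdrawal, leave the grounds for stopping the intervention as they are. Add that stopping it for safety or non-attendance does not end outcome collection. Feeding pattern, morbidity and the scales are still sought at 1, 4 and 6 months, or feeding status alone if the woman declines the rest, unless she withdraws consent to be contacted.
2. In Sample size, do not treat incomplete intervention due to prematurity as loss of the endpoint.
3. In Statistical analysis, reconcile the per-protocol statement with this. The extra data help only if women are also analysed in the arm to which they were randomised.

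If the full protocol already provides for such follow-up, items 1 and 2 amount to bringing the article into line with it.

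The cost is one paragraph, two short edits, and a brief call or message per affected woman at time points already scheduled. The downside is a few extra contacts with women who have left the intervention, subject to their consent.
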